#### **7.3.4 Interim analyses**

No interim analysis is planned during the course of the study.

### **7.4 HANDLING OF MISSING DATA**

Every effort should be made to collect complete data on each test day. Missing value from Visit 4 and 6 will not be imputed. Missing value of baseline (Visit 3 or 5) will be imputed with the value from the other baseline if available. If not available the patient will not be included in the FAS.

Methods to handle any exceptional cases will be considered only before unblinding and will be documented.

With respect to safety evaluation, it is not planned to impute missing data.

### **7.5 RANDOMIZATION**

This is a cross-over trial with two treatment periods. Patients who meet the in- and exclusion criteria will be randomized in blocks to double-blind treatment sequences (AB and BA) with a ratio of 1:1. BI will arrange for the randomization and the packaging and labeling of study medication.

The randomization list will be generated using a validated system, which involves a pseudo-random number generator so that the resulting treatment will be both reproducible and non-predictable. The block size will be documented in the CTR. Access to the codes will be controlled and documented.

Practical aspects of the treatment allocation process and methods to carry out blinding are detailed in Sections 4.1.2 and 4.1.5.

### **7.6 DETERMINATION OF SAMPLE SIZE**

Based on the post-hoc analyses of the GOLD stage II patients in previous parallel Studies 205.131 and 205.223, and recent publication (4), it is deemed reasonable to assume that the effect between once-daily administration of tiotropium with placebo on IC will be 100 ml in GOLD stage I / II patients, and the standard deviation of change from baseline will be 340 ml. By assuming a correlation,  $r$  between the changes from baseline of the two treatment periods for the same patient, the variance of the within-patient difference can be calculated as:  $\text{var1} + \text{var2} - 2 * r * \sqrt{\text{var1} * \text{var2}} = (340\text{ml})^2 + (340\text{ml})^2 - 2 * r * (340\text{ ml} * 340\text{ ml})$ , where var1 and var2 are the variances of the change from baseline in

the first and second treatment periods, respectively. Various combinations of correlation and power are used to feed in nQueryAdvisors 6.01 MOT0-1 (one-sample t-test) with the following results:

Table 7.6: 1                      Calculated power and associated sample size (SD=340 ml, delta=100 ml)

| Correlation | SD of within-subject difference
between two periods | Effect size  | Power     | N          |
|-------------|--------------------------------------------------------|--------------|-----------|------------|
| 0.3         | 402                                                    | 0.249        | 90        | 172        |
| 0.4         | 372                                                    | 0.268        | 90        | 148        |
| 0.5         | 340                                                    | 0.294        | 80        | 93         |
| 0.5         | 340                                                    | 0.294        | 85        | 106        |
| 0.5         | 340                                                    | 0.294        | 90        | 124        |
| 0.6         | 304                                                    | 0.329        | 80        | 75         |
| 0.6         | 304                                                    | 0.329        | 85        | 85         |
| 0.6  | 304                                             | 0.329 | 90 | 100 |

In a previous cross-over exercise Study 205.334, which comparing eight-weeks treatment with tiotropium plus salmeterol versus the fixed combination of fluticasone and salmeterol inpatients with COPD, only the first baseline value was collected. If the second baseline value is assumed to be the same as the first baseline, it showed a correlation of 0.5 between the two periods in terms of the change from baseline. However, this study had a relatively low correlation between the two post-dose IC values. Based on the information, it is deemed reasonable to assume a correlation of 0.6 between the changes from baseline of the two treatment periods.

Using a correlation of 0.6 and a type one error rate of 0.05 (two-sided), the sample size with 90% power to detect a 100 ml difference in IC change from baseline requires 100 patients in the analysis set. Assuming a drop-out rate of 20%, a total of 124 patients need to be randomized to ensure 100 completed, as well as to accommodate the block size of four in randomization.

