### **7.2 NULL AND ALTERNATIVE HYPOTHESES**

The treatment difference with tiotropium to placebo will be tested for isotime IC change from baseline at the level of  $\alpha = 0.05$  (two-sided). The primary hypothesis can be written as follows:

H0: Mean change from baseline of isotime IC after six weeks of treatment with tiotropium = Mean change from baseline of isotime IC after six weeks of treatment with placebo

H1: Mean change from baseline of isotime IC after six weeks of treatment with tiotropium ≠ Mean change from baseline of isotime IC after six weeks of treatment with placebo

Different baseline values will be used for the two treatment periods of the cross-over study.

Visit 3 will be the baseline for the first period, while Visit 5 (after wash-out) will be the baseline for the second period.

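### The 90% power rests on a correlation of 0.6 that the cited shared-baseline figure of 0.5 does not support, because this trial subtracts a separate baseline in each period

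*Protocol*

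**What the plan says.** Section 7.6 assumes that "the effect between once-daily administration of tiotropium with placebo on IC will be 100 ml" and that "the standard deviation of change from baseline will be 340 ml". It computes the variance of the within-patient difference from an assumed correlation between the two changes and applies a one-sample t-test. Table 7.6: 1 covers correlations from 0.3 to 0.6. The last row is chosen, and the text concludes that "90% power to detect a 100 ml difference in IC change from baseline requires 100 patients in the analysis set". With 20% drop-out, 124 patients are randomized.

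The correlation is taken from Study 205.334, which collected only a first baseline: "If the second baseline value is assumed to be the same as the first baseline, it showed a correlation of 0.5". The protocol then remarks that the two post-dose IC values in that study correlated rather weakly, and on that basis "it is deemed reasonable to assume a correlation of 0.6 between the changes from baseline of the two treatment periods".

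Section 7.2 says of the present trial: "Different baseline values will be used for the two treatment periods of the cross-over study". Visit 3 serves period 1, and Visit 5, after wash-out, serves period 2. Section 7.6 makes no allowance for this difference from Study 205.334.

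**The concern.** When the same baseline measurement is subtracted from both post-treatment values, its error enters both changes with the same sign. The two changes are then correlated for a reason unrelated to how repeatable the response is. A second, independently measured baseline breaks that link. A correlation from a shared-baseline calculation therefore cannot be carried over to a separate-baseline design, still less be raised.

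The correlation is the input that moves the sample size in Table 7.6: 1, and this is the only power statement for the primary endpoint. If it is too high, the trial has less power than stated, and a null result on isotime IC could be read as stronger evidence of no effect than the design can give.

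**Working it through.** **Inputs.** From Section 7.6: difference 100 ml, SD of change 340 ml in each period, two-sided alpha 0.05, N = 100, r = 0.6; source correlation 0.5 with one reused baseline. From Section 7.2: baselines at Visits 3 and 5.

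**1. The plan's own figure.** SD of the within-patient difference = 340 × √(2(1 − r)). At r = 0.6 this is 340 × √0.8 = 304 ml. An exact noncentral-t calculation gives N = 100 for 90% power (90.3%). All eight rows of Table 7.6: 1 reproduce.

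**2. Shared baseline.** Let B be a baseline value and Y a post-treatment value, with equal variances. Write rYY, rBB and rYB for the post-post, pre-pre and pre-post correlations, with rYB the same within and across periods. Then

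corr(Y1 − B, Y2 − B) = (rYY − 2rYB + 1) / (2(1 − rYB)).

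If rYY = rYB, the numerator is 1 − rYB and the result is exactly 0.5, however reliable or unreliable IC is. The 0.5 in Study 205.334 is thus what reusing the baseline produces unaided.

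**3. Separate baselines.**

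corr(Y1 − B1, Y2 − B2) = (rYY + rBB − 2rYB) / (2(1 − rYB)).

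This equals the shared-baseline value minus (1 − rBB) / (2(1 − rYB)). The subtracted term is positive whenever the baseline is measured with any variability, so a shared-baseline 0.5 translates to something below 0.5. If all correlations are equal, the subtraction is 0.5 and r = 0.

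**4. The reason given for 0.6.** Suppose post-dose values will correlate better here, enough to lift the shared-baseline figure to 0.6, with rBB = rYB. The separate-baseline value is then 0.6 − 0.5 = 0.1. To have r = 0.6 with separate baselines and rYY = rBB = a, one needs (a − rYB) / (1 − rYB) = 0.6: for example, a = 0.88 with rYB = 0.70, or a = 0.92 with rYB = 0.80. The protocol reports no such values.

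**5. Power at N = 100, by the plan's t-test.**

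| r | SD of difference (ml) | Power | N for 90% |
|---|---|---|---|
| 0.6 | 304 | 90.3% | 100 |
| 0.5 | 340 | 83.0% | 124 |
| 0.4 | 372 | 75.8% | 148 |
| 0.3 | 402 | 69.2% | 172 |
| 0.2 | 430 | 63.4% | 197 |
| 0.1 | 456 | 58.4% | 221 |
| 0 | 481 | 54.0% | 245 |

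Taken at face value, the observed 0.5 already requires 124 analysable patients, which is the number to be randomized before the assumed 20% drop-out.

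**6. The planned model.** Section 7.3.1 adds baseline as a covariate and subject as a random effect. Simulations of that model at N = 100, with the SD of change held at 340 ml and all correlations assumed, gave:

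| Like-for-like (pre-pre, post-post) | Pre-post | r, separate baselines | Simulated power |
|---|---|---|---|
| 0.5 | 0.5 | 0 | about 75% |
| 0.7 | 0.7 | 0 | about 67% |
| 0.9 | 0.9 | 0 | about 58% |
| 0.60 | 0.50 | 0.20 | about 87% |
| 0.75 | 0.60 | 0.38 | about 90% |
| 0.85 | 0.75 | 0.40 | about 90% |
| 0.90 | 0.84 | 0.38 | about 83% |

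Equal correlations set a ceiling. There the baseline difference carries no information on Y1 − Y2, whose variance is 2σ²(1 − rYB). That equals the variance of one change, 340². Even the ideal adjustment therefore leaves an SD of 340 ml and 83.0% power.

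**The case against.** The strongest reply has four parts.

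- **No number is miscalculated, and 0.6 is labelled as an assumption.** Table 7.6: 1 already shows sample sizes down to r = 0.3. This is right, and the point should not be filed as an arithmetic error. But the flat 90% is carried forward from one row, and the reasoning offered for that row does not hold.
- **A better post-dose correlation does raise the correlation of changes under either baseline scheme.** That is true in direction. It does not replace the component lost when the baseline is no longer shared (step 4).
- **Equal correlations are not established.** Visits 3 and 5 are tested pre-dose, and Visits 4 and 6 about 2 hours 15 minutes after dosing. Like-for-like tests may well correlate more strongly than pre-post pairs, and r is then above 0. This stands. A reader might infer that the true correlation is about 0 and the true power 54%. The documents do not support that, because they report none of the correlations needed.
- **The t-test is not the primary analysis.** The baseline covariate recovers part of the loss, and in some plausible structures power reaches about 90%. This also stands. A reader might infer that 100 patients cannot deliver 90% power; the documents do not show that either. The t-test figures alone would understate the planned analysis.

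**Conclusion.** The point holds as a gap in justification. The only cited evidence for the correlation comes from a calculation with a shared baseline, and this trial does not share its baseline. That evidence points below 0.5, so neither the move to 0.6 nor the 90% power at 100 patients is supported. The direction follows from the algebra, given similar variances across visits and similar pre-post correlations within and across periods.

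The size is uncertain. With the SD of change held at 340 ml, the sizing t-test gives 54% at r = 0 to 83% at r = 0.5. The planned model gives about 58% to 75% under equal correlations, and about 83% to 91% where like-for-like correlations clearly exceed pre-post. All these correlations are assumptions. The 90% is unsupported, not impossible.

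This should be fixed but is not critical: the hypothesis, estimate, confidence interval and type I error are unaffected.

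**What to change.** Keep the sample size. In Section 7.6:

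- remove the step from Study 205.334 to 0.6, and say that its 0.5 was obtained with a single reused baseline;
- state the correlation for separate Visit 3 and Visit 5 baselines as an assumption with a range of 0 to 0.5;
- replace the flat 90% with the power of 100 analysable patients over that range, given both for the t-test used for sizing and for the planned baseline-adjusted mixed model, with the assumed between-visit correlations listed.

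The cost is one rewritten paragraph, one table and a less favourable stated power. No patients are added, and the planned analysis does not change.

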## 8. ADMINISTRATIVE MATTERS

The trial will be carried out in compliance with the protocol, the principles laid down in the Declaration of Helsinki, version as of October 1996 (as long as local laws do not require to follow other versions), in accordance with the ICH Harmonised Tripartite Guideline for Good Clinical Practice (GCP) and relevant BI SOPs. Standard medical care (prophylactic, diagnostic and therapeutic procedures) remains in the responsibility of the treating physician of the patient.

Insurance Cover: The terms and conditions of the insurance cover are made available to the investigator and the patients via documentation in the ISF (Investigator Site File).

### 8.1 ETHICS

#### 8.1.1 Independent Ethics Committee or Institutional Review Board

The trial will not be initiated before the protocol and informed consent and patient information form have been reviewed and received approval / favourable opinion from the local Institutional Review Board (IRB) / Independent Ethics Committee (IEC) and, for other countries, as required by local laws and regulations approval by / notification to the regulatory authority. Should a CTP amendment be made that needs IRB / IEC approval and authority notification/approval, the changes in the CTP will not be instituted until the amendment and revised informed consent (if appropriate) have been reviewed and received approval / favourable opinion from the local IRB / IEC and, for other countries, as required by local laws and regulations the regulatory authority has been notified / provided approval. A CTP amendment intended to eliminate an apparent immediate hazard to patients may be implemented immediately providing that the regulatory authority and IRB / IEC are notified as soon as possible and an approval is requested. CTP amendments exclusively for logistical or administrative changes may be implemented with notification to the IRB / IEC.

The constitution of the IRB / IEC must meet the requirements of ICH GCP and of the participating countries. A list of the IRB / IEC members who attended the meeting when the CTP / CTP amendment was discussed, including names and qualifications, needs to be provided by the IRB / IEC to the investigator and to the sponsor. The investigator and the sponsor must provide to the regulatory authorities the name and address of the IRB / IEC along with a statement from the IRB / IEC that it is organised according to GCP and the applicable laws and regulations. The IRB / IEC must perform all duties outlined by the requirements of ICH GCP and of the participating countries.

#### 8.1.2 Patient Information and Informed Consent

Prior to patient participation in the trial, written informed consent must be obtained from each patient (or the patient's legally accepted representative) according to ICH GCP and to the regulatory and legal requirements of the participating country. Each signature must be personally dated by each signatory and the informed consent and any additional patient-information form retained by the investigator as part of the trial records. A signed

copy of the informed consent and any additional patient information must be given to each patient or the patient's legally accepted representative.

The patient must be informed that his / her personal trial-related data will be used by Boehringer Ingelheim in accordance with the local data protection law. The level of disclosure must also be explained to the patient.

The patient must be informed that his / her medical records may be examined by authorised monitors (CML / CRA) or Clinical Quality Assurance auditors appointed by Boehringer Ingelheim, by appropriate IRB / IEC members, and by inspectors from regulatory authorities.

Should a CTP amendment become necessary, the patient consent form and patient information form may need to be revised to reflect the changes to the CTP. It is the responsibility of the investigator and the sponsor to ensure that an amended consent form is reviewed and has received approval / favourable opinion from the IRB / IEC and for other regions, as required by ICH GCP and by local laws and regulations and the regulatory authority has provided approval / has been notified, and that it is signed by all patients subsequently entered in the trial and those currently in the trial, if affected by the amendment.

## **8.2 RECORDS**

### **8.2.1 Drug accountability**

Drug supplies, which will be provided by the sponsor, must be kept in a secure, limited access storage area under the storage conditions defined by the sponsor. Where necessary, a temperature log must be maintained to make certain that the drug supplies are stored at the correct temperature at all times.

The investigator and/or pharmacist and/or investigational drug storage manager must maintain records of the product's delivery to the trial site, the inventory at the site, the use by each patient, and the return to the sponsor or alternative disposition of unused product(s). These records will include dates, quantities, batch/serial numbers, expiry ('use by') dates, and the unique code numbers assigned to the investigational product(s) and trial patients. The investigator / pharmacist / investigational drug storage manager will maintain records that document adequately that the patients were provided the doses specified by the Clinical Trial Protocol (CTP) and reconcile all investigational product(s) received from the sponsor. At the time of return to the sponsor, the investigator / pharmacist / investigational drug storage manager must verify that all unused or partially used drug supplies have been returned by the clinical trial patient and that no remaining supplies are in the investigator's and/ or patient's possession.

### **8.2.2 Emergency code break**

For blinded trials an emergency code break will be available to the investigator / pharmacist / investigational drug storage manager. This code break may only be opened in emergency situations when the identity of the trial drug must be known to the investigator in order to provide appropriate medical treatment or if required to assure safety of trial participants. If the code break for a patient is opened, the sponsor must be informed immediately. The reason

for opening the code break must be documented on the envelope and appropriate electronic Case Report Form (eCRF) page along with the date and the initials of the person who broke the code.

### **8.2.3 Case Report Forms (CRFs)**

All of the clinical data will be captured via electronic data capture (EDC) using the Oracle Clinical Remote Data Capture system, a web-based tool. The investigator site staff will enter and edit the data via a secure network, with secure access features (username, password and secure identification or username and password – an electronic password system). A complete electronic audit trail will be maintained. The investigator will approve the data using an electronic signature (Ref: 21 CFR Part 11), and this approval is used to confirm the accuracy of the data recorded.

Electronic CRFs (eCRFs) will be used for all patients. The investigator's data will be accessible from the investigator's site throughout the trial. Relevant medical history prior to enrolment will be documented at the baseline visit. Thereafter during the trial, narrative statements relative to the patient's progress during the trial will be maintained. The electronic CRFs must be kept current to reflect patient status at each phase during the course of the trial. The patients must not be identified on the electronic CRF by name. Appropriate coded identification (i.e., Patient Number) must be used. The investigator must make a separate confidential record of these details (patient identification code list) to permit identification of all patients enrolled in a clinical trial in case follow-up is required. While a trial is ongoing and until the access to the database has been terminated, there will be no Documentation of Changes (DOCs). All changes will be requested from the investigator through the EDC system. If a change is necessary once the investigator has no further access to the database, a DOC will be sent to the investigator for confirmation of the change. The investigator's signature is requested to show he / she agrees with the change that was made. The original DOC is kept by the investigator.

Copies of the electronic CRF together with all data changes made will be supplied to the investigator at the end of the trial. The investigator will be responsible for retaining all records pertaining to the trial as specified in the appropriate contract.

### **8.2.4 Source documents**

Source documents provide evidence for the existence of the patient and substantiate the integrity of the data collected. Source documents are filed at the investigator's site.

Data reported on the CRFs or entered in the eCRFs that are transcribed from source documents must be consistent with the source documents or the discrepancies must be explained. The investigator may need to request previous medical records or transfer records, depending on the trial; also current medical records must be available.

For eCRFs all data must be derived from source documents.

- Patient identification (gender, date of birth)
- Patient participation in the trial (substance, trial number, patient number, date patient was informed)
- Dates of patient's visits, including dispensing of trial medication
- Medical history (including trial indication and concomitant diseases, if applicable)
- Medication history
- Adverse events (onset date [mandatory], and end date [if available])
- Serious adverse events (onset date [mandatory], and end date [if available])
- Concomitant therapy (start date, changes)
- Originals or copies of PFT, Exercise Tests, 12-lead ECG recording (Visit 1) and laboratory results (in validated electronic format, if available).
- Originals or copies of questionnaires (BDI Dyspnea index focal score, Modified Borg Scale, VSAQ, WPAI questionnaire and FACIT short form) and patient diary.
- Conclusion of Patient's Participation in the trial

### **8.2.5 Direct access to source data - documents**

The investigator / institution will permit trial-related monitoring, audits, IRB / IEC review and regulatory inspection, providing direct access to all related source data / documents. CRFs / eCRFs and all source documents, including progress notes and copies of laboratory and medical test results must be available at all times for review by the sponsor's clinical trial monitor, auditor and inspection by health authorities (e.g., FDA). The Clinical Research Associate (CRA) / on-site monitor and auditor may review all CRFs / eCRFs, and written informed consents. The accuracy of the data will be verified by reviewing the documents described in Section 8.2.4.

